# 2. Materials and Methods

## 2.1 Participant Selection

### Total Numbers of Participants and Study Duration

One hundred and twenty (120) evaluable participants will be recruited to the study, randomised between three groups. The duration of the study will be 15 days (+/- 1 day), Day 0 being the first treatment day, with 14 days follow up.

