### 2.3.2 Randomisation

The randomised treatment allocation code will be generated using the free online randomisation service provided at <http://www.randomization.com/>. The treatment allocation will be made in 11 balanced blocks of 12 treatments and the Seed number and date of randomisation will be recorded on the randomisation plan.

The treatment allocations will be prepared as sheets bearing the identification of the product to be used and instructions for application of the relevant product. The product identification/instruction sheets will be sealed in opaque envelopes numbered sequentially on the outside with the participant number taken from the randomisation schedule. Each envelope will be enclosed in a CRF prior to use. Each investigator delegated to enrol participants will allocate the numbered CRFs to participants in numerical sequence. However, where two or more investigators, each allocated separate blocks of numbers, enrol participants in parallel the overall numerical sequence will not follow chronologically.

Only after written informed consent has been obtained will the investigator allocate a study number and open the randomisation envelope for that number. The investigating team will keep a second batch of envelopes, and a copy of the randomisation code also in a sealed envelope, in case an adverse event, reaction, or any other emergency circumstance necessitates that the code be broken.

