## 3.4 Statistical Methods

Sample Size Determination:

The study has been designed to confirm that KindaPed AF (5% 1,2-octanediol alcohol free lotion) has an essentially similar efficacy comparable to that of KindaPed lotion (5% 1,2-octanediol with 20% alcohol). It is not designed as a full equivalence study but is designed to be able to identify any significant differences between the treatments in pair wise comparisons.

This study is based upon the same sample size as that used in four previous studies of head louse treatments conducted on behalf of Thornton & Ross Ltd (CTMK06, CTMK08, CTMK09, and CTMK10) for basic comparative purposes and is estimated to provide adequate data for demonstration of effect. The actual sample size of 40 per group makes allowance for dropout. Comparison of the results from this study can be made with the results from those studies with respect to similarities of population demographics, and with previous studies of 1,2-octandiol lotion (CTEP01 and CTEP02) with respect to efficacy outcome and acceptability.

Interim analysis

It is proposed to conduct an interim analysis of treatment outcome only after enrolment and completion of sixty (60) participants (approximately 20 in each group). This analysis will be conducted blind of treatment allocation using outcome data entered into a spreadsheet which would then be overlaid with treatment allocation identified only as “a”, “b”, or “c”. This will enable the Sponsor to identify whether one treatment is performing exceptionally well or exceptionally poorly and allow them to make a decision in good time whether they wish to extend or to curtail any aspect of the study. The results of this analysis will be conveyed to the Sponsor in narrative form only.

Analytical Methods:

The primary endpoint is the frequency of cure tested using the "intention-to-treat" population in comparison with the body of data obtained during previous studies using overnight or 2-2.5 hour application times for the product. Secondary endpoints will be the frequency of ovicidal failure and of reinfestation and the numbers of lice seen at the different assessment times. Other endpoints will be the safety of the product and participant acceptance.

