Analyses will be conducted based on both the "intention-to-treat" and the "per-protocol" populations. The study group will be compared with study groups from previous studies in which participants were treated using an 8 hour/overnight treatment or a 2-2.5 hour treatment on baseline characteristics, safety, acceptability, and efficacy using Fisher's exact test for yes/no variables and the Mann-Whitney U test for ranked variables. Where analysis shows important differences in baseline characteristics, chi squared and rank tests stratified for these characteristics may also be conducted. 95% confidence limits will be presented for the difference between this study group and previous groups in the primary endpoint.

These analyses will be used to determine whether the study provides evidence of essential similarity between KindaPed AF (5% 1,2-octanediol alcohol free lotion) and KindaPed (5% 1,2-octanediol lotion) in the elimination of infestation.

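### Fisher's exact test, if used for the randomised 40 v 40 comparisons, runs at no more than 3.3% and gives up about 5 to 7 points of power in a trial that hopes to conclude similarity (minor)

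*Protocol*

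**What the plan says.** All of this stands in Protocol section 3.4 unless noted.

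- **Test.** Yes/no variables, efficacy among them, get Fisher's "exact test for yes/no variables and the Mann-Whitney U test for ranked variables". Chi-squared and rank tests appear only as optional stratified analyses if baseline differences are found. Cure, the primary endpoint (section 3.1.2), is a yes/no variable.
- **Comparison to which the test is attached.** The same sentence opens: "The study group will be compared with study groups from previous studies in which participants were treated using an 8 hour/overnight treatment". The sizes of those earlier groups are not given.
- **Comparison between randomised groups.** The sample-size text says the study is not a full equivalence study but "is designed to be able to identify any significant differences between the treatments in pair wise comparisons". No test is tied to these comparisons.
- **Interval.** "95% confidence limits will be presented for the difference between this study group and previous groups in the primary endpoint".
- **Numbers.** "The actual sample size of 40 per group makes allowance for dropout". Section 2.1 has 120 evaluable participants in three groups, and section 2.3.2 has 11 balanced blocks of 12.
- **Conclusion sought.** The analyses are to decide whether there is evidence that the two products are essentially similar. No margin, significance level, cure rate or power is stated.

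**The concern.** Fisher's test conditions on the total number of cures. With small, equal groups and high cure rates few tables can reach p ≤ 0.05, so the test rejects far less often than its nominal level allows. In a superiority trial that works against the sponsor's claim. Here the hoped-for answer is that the alcohol-free product is as effective as the original, and no margin says how large a difference would count against that. A test that under-rejects then leans towards the hoped-for answer. At stake is a modest and avoidable loss of ability to detect a real difference between formulations.

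**Working it through.** **Inputs.** From the protocol: Fisher's test; three groups; 120 / 3 = 40 per group. Assumed: a two-sided 5% level (in line with the 95% limits), cure rates of 50-95%, and earlier groups of 80, 120 or 200.

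**The plan's own figure.** The 40 per group is carried over from earlier studies and cannot be reproduced, because no level, power or cure rates are given. For scale only, 80 v 50% cure at two-sided 5% and 80% power gives n = [1.96√(2 × 0.65 × 0.35) + 0.84√(0.8 × 0.2 + 0.5 × 0.5)]² / 0.30² ≈ 39 per group.

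**Why the test under-rejects.** Take 40 of 40 cured in one group and 35 of 40 in the other. Fisher's two-sided p is 2 × C(40,5)/C(80,5) = 2 × 658,008 / 24,040,016 = 0.055, so even the most extreme split of five failures does not reject. With six failures it is 2 × C(40,6)/C(80,6) = 2 × 3,838,380 / 300,500,200 = 0.026. At 95% cure only 80 × 0.05 = 4 failures are expected in total, so rejection is rarely possible at all.

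**Method.** All 41 × 41 tables were enumerated. Fisher's p is the sum of the hypergeometric probabilities no larger than that of the observed table.

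- Size(π) = Σ Bin(x₁; 40, π) Bin(x₂; 40, π) over rejecting tables.
- Power(π₁, π₂) is the same sum with the two rates.
- Boschloo's test uses Fisher's p as its statistic, with the largest cut-off that keeps the maximum size over π = 0.001 to 0.999 at or below 5%. At 40 v 40 that cut-off is 0.0707 and the maximum size is 4.8%.

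**Fisher's true size at 40 v 40.** Maximum 3.3% (at 50% cure); 2.8% at 70%, 2.9% at 75%, 2.8% at 80%, 1.7% at 90%, 0.4% at 95%.

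**Power at 40 v 40.**

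| Cure rates | Fisher | Boschloo | Gain (points) |
|---|---|---|---|
| 90 v 70% | 53.4% | 59.2% | 5.8 |
| 80 v 60% | 40.8% | 47.6% | 6.8 |
| 95 v 80% | 41.1% | 48.4% | 7.3 |
| 85 v 70% | 28.1% | 33.5% | 5.4 |
| 90 v 80% | 16.2% | 20.0% | 3.8 |

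Boschloo's rejection region contains Fisher's, so it is never less powerful. Uncorrected Pearson chi-squared gains more, but its size reaches 5.9%.

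**Sensitivity to group size.** For the first four pairs, 36 v 36 (assumed 10% dropout) gives a gain of 8.5-12.6 points. The randomisation list (11 × 12 = 132, or 44 per group) gives 7.3-8.8 points. The gain moves with n because the tests are discrete.

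**Against larger previous groups.** At 40 v 80, 40 v 120 and 40 v 200, Fisher's maximum size is 4.1%, 4.45% and 4.3%. It is 3.1-3.6% at 90% cure and 2.6-2.9% at 95%. For the same four pairs, taken in either direction, Boschloo gains 0.3-4.1 points; for example 69.6% to 71.3% at 40 v 80 with 90 v 70% cure.

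**The case against.** The strongest objection is that the sentence naming Fisher's test is about previous-study groups, so 40 v 40 is not the comparison to which the protocol attaches it. That stands as a limit on the figures: with larger earlier groups most of the shortfall goes. But section 3.4 also promises pairwise comparisons between treatments, and no other test is named for unstratified yes/no data, so 40 v 40 is a reasonable case to examine.

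Fisher's test is also valid, prespecified and standard, and it controls type I error. That stands in full: its conservatism is a known trade-off, not an error.

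A reader might infer that a non-significant result will be declared similarity. The protocol states no such rule. It says that the analyses together, including 95% limits for the difference in the primary endpoint, will inform that judgement. What remains is narrower: those limits are described only against previous groups, and there is no margin to read them against. The interval method could be left to the statistical analysis plan, but which comparison carries the conclusion is already fixed here.

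Finally, another test of difference does not repair an inference of similarity. That is true, and it keeps the point small.

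**Conclusion.** The point holds in limited form. If Fisher's test is applied to the randomised groups at 40 v 40 and two-sided 5%, its true size is at most 3.3%. An exact test that still holds 5% would gain about 5-7 points of power for differences of 15 to 20 points. For the comparisons with previous groups that the sentence literally describes, the gain is about 0.3-4 points under the assumed group sizes. The level, cure rates and earlier group sizes are all assumptions.

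The documents do not support calling the test wrong, or saying that non-significance will be taken as similarity. The direction of the loss is unhelpful in a trial seeking similarity without a margin. Neither test makes 40 per group informative about a 10-point difference such as 90 v 80%. The point is minor and worth adopting because it costs little.

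**What to change.** In section 3.4:

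1. For cure and other yes/no outcomes in the concurrent randomised comparisons, replace Fisher's test with Boschloo's exact unconditional test, and state the significance level and that it is two-sided.
2. Make a score-based (Miettinen-Nurminen) 95% confidence interval for the randomised AF minus KindaPed difference in cure the main result, and rest the similarity conclusion on it. As there are two AF groups, name which difference is meant. Comparisons with previous studies can stay as supporting information.

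The cost is a change of wording; no extra participants are needed. The drawbacks are a less familiar test name and occasional disagreement between test and interval near the boundary, so the text should say that the interval governs. The second change matters more than the first.

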## 1.2 Rationale

Infestation with the human head louse (*Pediculus capitis*) has been at a high level within the European Union since the appearance of strains of head lice resistant to one or more of the currently available insecticidal products were first described (1, 2, 3). Families are aware of a resistance problem but have no way of knowing if the lice they are trying to eradicate are resistant to the product they are using. Many people have attempted alternative methods of treatment such as combing (4) but for the most hard pressed families (as described in reference 3) this frequently has a poor outcome with children suffering infestations for many months (5).

Given a choice, a majority of care givers would choose to use a safe and simple chemical treatment to eliminate infestation form their children. Various products have been introduced into the European market as class I Medical Devices based on their physical mode of action and their general safety profile.

KindaPed (5% 1,2-octanediol lotion) and KindaPed AF (5% 1,2-octanediol alcohol free lotion) are class I Medical Device preparations based upon a cosmetic moistening and spreading agent.

The original KindaPed (5% 1,2-octanediol lotion) was originally investigated in a large randomised controlled trial in 2007-08 in comparison with 0.5% malathion liquid. In this study KindaPed was shown to be significantly superior to malathion using applications times of 2-2.5 hours and 8 hours/overnight. However, the KindaPed preparation was formulated with 20% isopropanol, which it is believed was the cause of a number of mild adverse reactions on excoriated skin.

KindaPed AF (5% 1,2-octanediol alcohol free lotion) contains no alcohol and should not cause irritation even on excoriated skin. This clinical investigation is designed to confirm no loss of efficacy of Kindaped AF versus Kindaped.

Both 5% 1,2-octanediol lotion preparations are used with a repeat treatment applied after one week as recommended by The British National Formulary (BNF) for all currently available treatments.

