## Design in Brief

This is a randomised, controlled, assessor blind, study of two variants of the same class I Medical Device product for control of head louse infestation. One hundred and twenty (120) evaluable participants, minimum age 6 months^[[1]](#footnote-1)^, who upon examination are confirmed to have head lice and who fit the selection criteria (see section 2.1.2 and 2.1.3) will be recruited to the study.

At the first visit (Day 0), verbal consent will be obtained to check for the presence of live head lice using a fine-toothed plastic detection comb. After the preliminary assessment, participants can be enrolled to the study, provided they comply with the inclusion/exclusion criteria, and any further questions they may have are fully dealt with.

Participants (or their parents/guardians if they are aged below 16 years) will be asked to give written informed consent and sign a Consent Form before participation in the study. There will be a separate Assent Form for younger children capable of giving written assent. Children too young to give assent can be entered in the study on the consent of a parent/guardian. Assent Forms will be witnessed by the parent/guardian and signed by the Investigator. Consent will be sought for permission to inform the participant’s GP that their patient is taking part in the study. Other infested household members who are unable to participate in the study for any reason, e.g. not being available for the assigned follow up visits, will be offered a standard of care treatment (Hedrin 4% liquid gel) in order to reduce the risk of reinfestation of participants during the course of the study.

The Investigator will assign each participant a study number, this being the next available number allocated to that investigator from a randomised treatment allocation sequence. Participants will be divided between three groups as follows:

Group A: KindaPed AF (5% 1,2-octanediol alcohol free lotion ), applied for 2 hours (maximum 2.5 hours) before washing off using shampoo, with a repeat treatment one week later.

Group B: KindaPed AF (5% 1,2-octanediol alcohol free lotion ), applied for 8 hours (minimum) or overnight before washing off using shampoo, with a repeat treatment one week later.

Group C: KindaPed lotion (5% 1,2-octanediol lotion with 20% alcohol), applied for 2 hours (maximum 2.5 hours) before washing off using shampoo, with a repeat treatment one week later.

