## 3.3 Proposed Primary and Secondary Analyses

1. To compare efficacy of KindaPed AF (5% 1,2-octanediol alcohol free lotion) with KindaPed (5% octanediol lotion with 20% alcohol) for elimination of infestation by head lice.
2. To compare KindaPed AF (5% 1,2-octanediol alcohol free lotion) with KindaPed (5% octanediol lotion with 20% alcohol) with regard to prevention of louse egg hatching (ovicidal action) by monitoring the presence/absence of juvenile stages of lice following the first and second treatments.
3. To compare KindaPed AF (5% 1,2-octanediol alcohol free lotion) with KindaPed (5% octanediol lotion with 20% alcohol) To investigate 5% 1,2-octanediol alcohol free lotion with regard to participant acceptability.

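### The formulation conclusion is not tied to Group A versus Group C, the one randomised comparison with equal application times, and Section 3.4 rests it on historical comparisons not matched on time.

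*Protocol*

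**What the plan says.** Section 1.2 (Rationale) poses a question about formulation: "This clinical investigation is designed to confirm no loss of efficacy of Kindaped AF versus Kindaped".

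Design in Brief defines three randomised groups:
- "Group A: KindaPed AF (5% 1,2-octanediol alcohol free lotion ), applied for 2 hours (maximum 2.5 hours) before washing off using shampoo"
- "Group B: KindaPed AF (5% 1,2-octanediol alcohol free lotion ), applied for 8 hours (minimum) or overnight before washing off using shampoo"
- "Group C: KindaPed lotion (5% 1,2-octanediol lotion with 20% alcohol), applied for 2 hours (maximum 2.5 hours) before washing off using shampoo"

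The analysis text does not carry this structure forward. The first analysis in Section 3.3, on clearing the infestation, begins: "To compare efficacy of KindaPed AF (5% 1,2-octanediol alcohol free lotion) with KindaPed (5% octanediol lotion with 20% alcohol) for elimination of infestation by head". It names two products but no group and no application time. The aim in Section 1.1 and the objectives in Section 1.3 do the same.

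Under sample size, Section 3.4 says the study should be able to find differences between treatments in pairwise comparisons, without saying which pair decides. Under analytical methods, the same section tests the primary endpoint (cure, intention-to-treat) against data from previous studies that used either application time. It refers to a single study group, and it plans 95% confidence limits for the difference between that group and the previous groups. It then concludes: "These analyses will be used to determine whether the study provides evidence of essential similarity between KindaPed AF (5% 1,2-octanediol alcohol free lotion) and KindaPed".

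**The concern.** Only A versus C changes the formulation and nothing else. B versus C changes formulation and contact time together. A comparison of B with earlier groups treated for 2-2.5 hours does the same and adds the differences between studies. A comparison of A with earlier 8-hour or overnight groups is also unmatched, and there the longer contact would favour the older product.

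Because the conclusion names only products, any of these comparisons could be cited for it. If the alcohol-free lotion is weaker at 2 hours but recovers with longer contact, a comparison using Group B could look like similarity although efficacy has been lost. Section 3.4 makes this more likely: it disclaims a full equivalence design and looks for significant differences, so finding none in a diluted comparison may be read as support. The claim at stake is the trial's headline claim.

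**Working it through.** **Inputs from the protocol.** A: 2 h, maximum 2.5 h. B: 8 h minimum or overnight. C: 2 h, maximum 2.5 h (Design in Brief). Size: 120 in three groups, 120/3 = 40, which agrees with the 40 per group in Section 3.4. That section states no cure rates, power, margin or alpha, so the sample size cannot be re-derived further.

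**Step 1: what each comparison changes.**

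| Comparison | Randomised and concurrent | Same application time | Formulation differs |
|---|---|---|---|
| A versus C | yes | yes | yes |
| B versus C | yes | no | yes |
| A versus B | yes | no | no |
| A versus earlier KindaPed, 2-2.5 h | no | yes | yes |
| B versus earlier KindaPed, 8 h/overnight | no | yes | yes |
| A or B versus earlier KindaPed at the other time | no | no | yes |

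Only the first row is randomised, matched on time and about formulation. In B versus C the ratio of contact times is at least 8/2.5 = 3.2. That is a ratio of times, not a bias in cure rate.

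**Step 2: which rows the text points to.** The written analyses in Section 3.4 are the historical rows, matched or not. The pairwise sentence covers the first three rows without ranking them. Nothing assigns the conclusion to the first row.

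**Step 3: possible size.** The protocol gives no effect of contact time, so every rate here is assumed. Take C = 80% and A = 60%, and let 8-hour contact recover none, half or all of the 20-point loss. The last two columns give the exact probability that Fisher's test is significant with 40 per group (two-sided 0.05 assumed).

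| B cure | A minus C | B minus C | A versus C significant | B versus C significant |
|---|---|---|---|---|
| 60% (no recovery) | -20 points | -20 points | 41% | 41% |
| 70% (half) | -20 points | -10 points | 41% | 12% |
| 80% (full) | -20 points | 0 points | 41% | 3% |

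Over a wider assumed grid (C at 70, 80 or 90%; loss of 10, 20 or 30 points) with full recovery, B versus C is significant in about 2-3% of trials whatever the loss. A versus C is significant in 11-85%. With no recovery the two comparisons behave alike.

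**Step 4: precision of the right comparison.** For A = 60% and C = 80%, the 95% half-width is 1.96 × √(0.6×0.4/40 + 0.8×0.2/40) = 1.96 × √0.010 = 0.196, about 20 points. With equal rates, 1.96 × √(2p(1-p)/40) gives 20 points at p = 70%, 17.5 at 80% and 13 at 90%. Naming A versus C estimates the right quantity but does not make the estimate precise.

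**The case against.** The strongest reply is that the design already contains the answer: A versus C is randomised, concurrent and matched on time, and pairwise comparisons are foreseen. This stands. A reader might infer from the 8-hour arm that formulation and contact time are inseparably confounded in this trial. They are not; the gap is that the conclusion is not assigned to the comparison that separates them.

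A reader might also infer that A and B will be pooled, because the objectives speak of KindaPed AF as one product. No section says so. Three groups are kept throughout, and the interim analysis labels them separately. With B at 80% pooling would halve the assumed loss, since (60+80)/2 = 70% is 10 points below 80%. That is not a planned analysis, and if longer contact recovered nothing, pooling would raise the chance of detection (60% against 41%).

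It is also true that KindaPed was studied earlier at both application times (Section 1.2), so an 8-hour comparator exists outside this trial. It is not randomised against Group B, however, and Section 3.4 does not match B to it.

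Finally, the deciding pair could be left to a statistical analysis plan. That would answer mere silence. Here the protocol itself directs the primary test, the confidence limits and the conclusion to historical groups at either time, and an analysis plan that named A versus C would have to depart from that text.

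**Conclusion.** The point holds as a badly fixed conclusion rule, not as a flaw in the arms. Followed as written, Section 3.4 allows an effect of longer contact to be credited to the formulation, through B versus C or through historical comparisons unmatched on time.

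How much could be hidden is unknown. It ranges from nothing, if longer contact adds no efficacy, to the whole loss, if it compensates fully. The 20-point example and its probabilities rest on assumed cure rates and an assumed two-sided 0.05 level. What comes from the protocol is the mismatch in application time and the absence of a deciding comparison.

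It would go too far to say that B versus C has no legitimate use. It is a valid randomised comparison of two regimens and fits the stated wish to learn about routine usage. It is simply not evidence that the formulations are similar.

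**What to change.** In Sections 3.3 and 3.4:

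1. Name Group A versus Group C (cure, intention-to-treat, difference with 95% confidence limits) as the comparison that supports the conclusion on formulation.
2. Reword the analytical methods so that comparisons with previous studies are supportive only and matched on application time: A with earlier 2-2.5 hour groups, B with earlier 8-hour or overnight groups. Replace the single study group with the named groups. Without this change, step 1 would leave Section 3.4 contradicting itself.
3. Report B versus C as a comparison of regimens and A versus B as the effect of application time within KindaPed AF, neither as evidence of formulation similarity.

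Settle this before the interim analysis at 60 participants, so that the choice cannot be influenced by results.

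The cost is wording only: arms, application times, participants and visits stay as they are. The price is that a favourable B versus C or historical result can no longer carry the headline claim alone, and the claim then depends on a comparison with about 40 per group.
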